### Primary outcome

The primary outcome is the time taken to discontinuation of NIV in patients with acute, severe exacerbations of COPD through the addition of ECCO_2_R to standard care. The definition of discontinuation of NIV is cessation of NIV for at least 6 h. Time to discontinuation will be measured from randomisation. The reason for discontinuation will be collected and successful discontinuation consists of being free of mechanical ventilation.

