### Secondary outcome

Secondary outcomes include the impact of ECCO2R on:Safety, including:Incidence of haemorrhagic complications—significant haemorrhage is defined as bleeding requiring transfusion of more than one unit of blood, intracerebral bleeding, bleeding requiring procedural interventionIncidence of thrombosis—all patients will have screening duplex ultrasound of the cannulated vesselIncidence of haemolysis defined by rising lactate dehydrogenase, bilirubin red cell fragments on a blood film and/or a rising plasma free-haemoglobin (> 0.5 g/dL)Complications relating to cannulation including those at insertion—bleeding, vascular damage, pneumothorax and line infection, both clinically apparent (erythema/cellulitis at insertion site) and microbiologically proven (positive blood culture with concomitant line tip culture or line insertion site culture)Physiology, including respiratory rate, heart rate, blood pressure, temperature, arterial blood gases measured at time (T)0 min, T30 minutes, T 60 min, then every fourth hour for the first 24 h and then every sixth hour until discontinuation of the acute phase of the trialDaily spirometry including forced vital capacity, forced expiratory volume in 1 s and the ratio between themWork of breathing, including electrical impedance tomography, parasternal electromyography and oesophageal pressure (these are described in detail below)Patient outcomes:Mortality (ICU, hospital and 3 month)Length of stay (ICU, hospital)Need for intubation and where this occurs, duration of mechanical ventilation and need for tracheostomy, NIV failure and need for intubation will be decided by the clinical team managing the patient. Reason for NIV failure will be recorded by the research team.3-Month hospital readmission rateTolerance, assessed using both a numerical rating scale (0–10) and visual acuity scale (0–10 cm) for both dyspnoea and comfort with the lowest reading being extremely uncomfortable and the highest being extremely comfortable. Comparisons between the two different measures will be used without an absolute definition of comfort/discomfort.At 3-months following randomisation: COPD assessment test, St George’s Respiratory Questionnaire, EuroQoL 5D. Comparisons between the different measures will be used without an absolute definition of success at follow-up.Cost-effectiveness with ICU bed day and consumables cost/quality adjusted life year (QALY)

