### Randomisation and codebreaking

Randomisation will be achieved using a computer-generated random list then stored as sequential sealed envelopes accessible to the primary study team. Other sites will randomise by telephone to the lead centre with envelopes opened and accessible only to the primary study team. The study participants, care providers and outcome assessors will be unblinded (open label).

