### Treatment of trial participants

Following presentation, initial medical therapy and NIV will be commenced as per current local and UK national guidelines for the management of AECOPD [47]. All patients with AECOPD and pH < 7.30 after a minimum of 1 h NIV will be eligible for inclusion unless exclusion criteria are met. Once informed written consent is obtained from either the patient or their consultee if consent from the patient is not possible, patients will be randomised to the continuation of NIV alone or addition of ECCO_2_R to NIV. All other aspects of care, including acute, on-going and post-trial care, will be at the discretion of the clinical team. Monitoring will be the standard of care of ICU, including arterial and central venous access where this is deemed appropriate by the clinical team.

Patients who are randomised to continuation of NIV alone will be managed in accordance with hospital protocols and national guidelines for NIV. NIV will be titrated to achieve an arterial pH > 7.35, respiratory rate < 25 and patient comfort with breathing. Discontinuation of NIV will occur when judged appropriate by the patient’s clinician. Cessation of NIV will be defined as occurring after six continuous hours without NIV.

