## Statistical analysis

Summary measures for the baseline characteristics of each group will be presented as mean and standard deviation for continuous (approximate) normally distributed variables, medians and interquartile ranges for non-normally distributed variables, and frequencies and percentages for categorical variables. The planned primary efficacy analyses, difference between the two arms in reduction in NIV duration, will be analysed on randomized patients using a non-parametric approach, Mann-Whitney U test. Similar analyses as for the primary outcome measure will be conducted for secondary efficacy data. Missing data in the efficacy population will not be interpolated. All randomised participants in both arms with valid non-invasive ventilation data will be included in the analysis. Analysis of the physiological data will be per protocol, whilst analysis of outcomes will be intention to treat. Physiological data will be compared within individuals to describe a relative change in work of breathing. The statistical analysis plan can be accessed through the corresponding author. No subgroups have been planned.

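### NIV stopped for palliation, refusal, intolerance or deterioration without intubation scores as a short, favourable time, because neither the success definition nor the primary analysis uses the reason

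*Protocol article*

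**What the plan says.** Primary outcome section of the protocol article: "The primary outcome is the time taken to discontinuation of NIV in patients with acute, severe exacerbations of COPD". Time runs from randomisation. The event is "The definition of discontinuation of NIV is cessation of NIV for at least 6 h", and then: "The reason for discontinuation will be collected and successful discontinuation consists of being free of mechanical ventilation".

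Treatment of trial participants leaves the decision to stop with the treating team: "Discontinuation of NIV will occur when judged appropriate by the patient’s clinician". Randomisation and codebreaking states that participants, carers and outcome assessors all know the allocation.

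Exclusion criteria removes patients with treatment limits only where those limits rule out critical care. A patient accepted to critical care but not for intubation can therefore be randomised. Patient refusal appears in the same list as an entry criterion and does not deal with refusal after randomisation.

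Secondary outcome has a separate item: "NIV failure and need for intubation will be decided by the clinical team managing the patient". The reason for NIV failure is to be recorded by the research team.

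Statistical analysis gives the primary comparison as "difference between the two arms in reduction in NIV duration, will be analysed on randomized patients using a non-parametric approach, Mann-Whitney U test". The analysis set is: "All randomised participants in both arms with valid non-invasive ventilation data will be included in the analysis".

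**The concern.** A short time on NIV is meant to signal recovery. As written, it can also signal the opposite. A patient who will not tolerate the mask, or whose NIV is withdrawn for comfort care, meets the 6 h rule and is not mechanically ventilated. That patient is labelled a success and enters the primary test with a short time. In a patient not for intubation, failure does not lead to mechanical ventilation, so the one event that denies success hardly ever occurs. The same patient cannot contribute to the intubation rate.

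Such stops rest on tolerance and judgement in an open-label trial, so their number can differ by arm. With 12 patients per arm, one or two are enough to matter. They could hide a real effect or produce an apparent one.

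**Working it through.** **1. How each way of stopping NIV is handled**

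| What happens | Success status under Primary outcome | Entry in the Mann-Whitney test |
|---|---|---|
| Recovers, off NIV for 6 h | Success | Duration |
| Refuses or cannot tolerate the mask, not intubated | Success | Short duration |
| NIV withdrawn for palliation, survives 6 h | Success | Short duration |
| Deteriorates, NIV stopped, not for intubation | Success | Short duration |
| Intubated | Not a success | Short duration; no other rule stated |

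Rows two to four are misclassified by the success definition. The last row is classified correctly, but the analysis does not use the classification. The two sections therefore have to be corrected together. The article does not define mechanical ventilation; its abstract uses the term for ventilation after NIV fails. Reading it to include NIV would change nothing, because NIV has already stopped.

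**2. The plan's own power figure**

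Inputs from Sample size: 48 h against 36 h, SD 10 h, 12 per arm, alpha 5%. The standardised difference is 12/10 = 1.2. A two-sided two-sample t-test then has 80.2% power, which reproduces the stated 80%. The planned Mann-Whitney test has about 77% on the same inputs (simulation, normal durations).

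**3. Effect of stops that are not recovery**

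The number and timing of these stops are assumptions, because the article gives neither. In the early scenario, stops are uniform on 6–24 h, with mean (6 + 24)/2 = 15 h.

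Expected difference in means, early stops:
- One control patient: (11 × 48 + 15)/12 = 45.25 h; 45.25 − 36 = 9.25 h.
- Two control patients: (10 × 48 + 2 × 15)/12 = 42.5 h; 42.5 − 36 = 6.5 h.
- One in each arm: the ECCO2R mean is (11 × 36 + 15)/12 = 34.25 h; 45.25 − 34.25 = 11.0 h.

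Power of the Mann-Whitney test (simulated, two-sided 5%):

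| Stops | Timing | Power |
|---|---|---|
| None | – | about 77% |
| One control | 6–24 h | about 53% |
| Two control | 6–24 h | about 22% |
| One in each arm | 6–24 h | about 61% |
| Two in each arm | 6–24 h | about 39% |
| Two control | 6–72 h | about 60% |
| Two control | 24–72 h | about 73% |

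Stops uniform on 24–72 h average (24 + 72)/2 = 48 h, the same as the control mean, so the mean difference stays at 12 h.

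No true effect (48 h in both arms), stops at 6–24 h in the ECCO2R arm only:
- None: about 2% of trials are significant in favour of ECCO2R.
- Two: about 7%.
- Three: about 12%.

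**4. What ranking failures worst would do**

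With a true effect and two failures in the control arm only, power is about 88%. With no true effect and three failures in the ECCO2R arm only, findings in favour of ECCO2R essentially disappear. With two failures in each arm, power is about 37–38%, close to the 39% above. Worst ranking therefore puts failures on the right side of the comparison, but it does not recover power when they are balanced.

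**The case against.** The strongest objection is that the primary test never uses the success label. The outcome is time to 6 h off NIV, and success is a separate descriptor. This stands. A reader might infer that the success sentence alone produces the losses of power, but the documents do not support that: the losses arise because the analysis ranks every duration alike. Rewording success without changing the analysis would leave each short time at its favourable rank.

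Second, the protocol does record NIV failure as judged by the clinical team, with its reason, and it collects ICU, hospital and 3-month mortality. This also stands. It would be wrong to infer that failure in a patient not for intubation goes unrecorded. But the item is secondary and nothing links it to the primary endpoint.

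Third, early stops confined to one arm are an unfavourable case. Patients expected to die within 24 h are excluded, which makes very early palliation less likely, though not refusal or intolerance. This stands, and is why a range is shown.

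Fourth, the statistical analysis plan, which is not shown, may set out how reasons for stopping enter the analysis. That is possible. The point here is not missing detail: the article states a definition of success, and a plan that applied it faithfully would misclassify these patients.

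**Conclusion.** The point holds for the success definition and the primary analysis taken together. Stops that are not recovery count as short, favourable times, and patients not for intubation can hardly be classed as unsuccessful.

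The size is conditional. It rests on normal durations with the protocol's means and SD, and on assumed numbers and timing of stops. Across the scenarios with one or two such stops in the control arm, or one in each arm, power ranges from about 22% to about 73%, against about 77% with none. Timing matters most: two late control stops cost little, two early ones a great deal.

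A reader might go further and conclude that the trial's result will be biased, or that a benefit of several hours would be created. The documents do not support this. They give no frequency of such stops and no evidence of imbalance between arms. A shift in means is also not what the rank test assesses; the relevant figures are the false-positive rates of about 7% and 12%, and they need two or three early stops in the ECCO2R arm alone. The correction is worth making before analysis, but it does not show the design to be unsound.

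**What to change.** - **Primary outcome:** define success as being alive and off both NIV and invasive ventilation for the stated period because support is no longer needed, judged from the reason already collected. Class stops for palliation, refusal, intolerance or deterioration as NIV failure, alongside intubation and death.
- **Statistical analysis:** state that failures, including intubation and death, take the worst rank in the Mann-Whitney test. Keep the duration analysis as now written as a sensitivity analysis.
- **Baseline and reporting:** record whether each patient is for intubation. Beside the intubation rate, report a combined outcome of intubation, or NIV failure in a patient not for intubation.

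These changes concern outcome classification and analysis only; they do not alter care. The cost is a few sentences in two sections and one baseline field. The primary endpoint becomes a composite of duration and failure and must be described as such, and the success rate will look slightly less favourable. As shown above, the change does not restore power when failures are balanced between arms.

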### Secondary outcome

Secondary outcomes include the impact of ECCO2R on:Safety, including:Incidence of haemorrhagic complications—significant haemorrhage is defined as bleeding requiring transfusion of more than one unit of blood, intracerebral bleeding, bleeding requiring procedural interventionIncidence of thrombosis—all patients will have screening duplex ultrasound of the cannulated vesselIncidence of haemolysis defined by rising lactate dehydrogenase, bilirubin red cell fragments on a blood film and/or a rising plasma free-haemoglobin (> 0.5 g/dL)Complications relating to cannulation including those at insertion—bleeding, vascular damage, pneumothorax and line infection, both clinically apparent (erythema/cellulitis at insertion site) and microbiologically proven (positive blood culture with concomitant line tip culture or line insertion site culture)Physiology, including respiratory rate, heart rate, blood pressure, temperature, arterial blood gases measured at time (T)0 min, T30 minutes, T 60 min, then every fourth hour for the first 24 h and then every sixth hour until discontinuation of the acute phase of the trialDaily spirometry including forced vital capacity, forced expiratory volume in 1 s and the ratio between themWork of breathing, including electrical impedance tomography, parasternal electromyography and oesophageal pressure (these are described in detail below)Patient outcomes:Mortality (ICU, hospital and 3 month)Length of stay (ICU, hospital)Need for intubation and where this occurs, duration of mechanical ventilation and need for tracheostomy, NIV failure and need for intubation will be decided by the clinical team managing the patient. Reason for NIV failure will be recorded by the research team.3-Month hospital readmission rateTolerance, assessed using both a numerical rating scale (0–10) and visual acuity scale (0–10 cm) for both dyspnoea and comfort with the lowest reading being extremely uncomfortable and the highest being extremely comfortable. Comparisons between the two different measures will be used without an absolute definition of comfort/discomfort.At 3-months following randomisation: COPD assessment test, St George’s Respiratory Questionnaire, EuroQoL 5D. Comparisons between the different measures will be used without an absolute definition of success at follow-up.Cost-effectiveness with ICU bed day and consumables cost/quality adjusted life year (QALY)

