**Methods/design:**

A randomised controlled open label trial of patients (12 in each arm) with acute exacerbations of COPD at risk of failing conventional therapy (NIV) randomised to either remaining on NIV or having ECCO_2_R added to NIV with a primary endpoint of time to cessation of NIV. The change in respiratory physiology following the application of ECCO_2_R and/or NIV will be measured using electrical impedance tomography, oesophageal pressure and parasternal electromyography. Additional outcomes, including patient tolerance, outcomes, need for readmission, changes in blood gases and biochemistry and procedural complications, will be measured. Physiological changes will be compared within one patient over time and between the two groups. Healthcare costs in the UK system will also be compared between the two groups.

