### Data collection

For eligible patients, clinical details will be collected after consent has been obtained and randomisation undertaken (Fig. 1). This will include details to confirm eligibility and basic demographic and medical details, including acute and chronic co-morbidity and medicines as well as a full physical examination. Details of baseline routine clinical investigations will be recorded. Participants will be allocated a sequential trial number to ensure participant anonymity and confidentiality. All data will be stored in de-identified password-protected databases held within the NHS. All paper documents will be transferred to the department of Critical Care at Guy’s and St Thomas’ NHS Foundation trust and stored in locked, fire-proof cabinets. All data transfers between institutions will conform to the information governance requirement of the NHS.

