#### ECCO_2_R

Patients who are randomised to addition of ECCO_2_R will undergo cannulation in either the right internal jugular vein or one of the femoral veins using a 15.5 French double lumen ECCO_2_R cannula (patient and operator preference) using an ultrasound-guided Seldinger technique. The ECCO_2_R device, will be primed with 0.9% saline and 1 unit/mL heparin in accordance with the manufacturer’s instructions. The blood flow will be titrated to the maximum achievable (usually 400–500 mL/minute) and sweep gas titrated up to 10 L/minute in 1 L/minute increments every 15 min. ECCO_2_R will be titrated to achieve an arterial pH > 7.35, respiratory rate < 25 and patient comfort with breathing. Discontinuation of NIV and ECCO_2_R will occur when judged appropriate by the patient’s clinician. Cessation of ECCO_2_R will be defined as occurring after six continuous hours without ECCO_2_R. All patients receiving ECCO2R will receive a continuous infusion of heparin to maintain an APTTr of 1.5–2 titrated using the hospital protocol. Data relating to the ICU inpatient stay will be collected from the ICU and hospital information systems. At 3 months following randomisation, a telephone interview will be conducted by the randomising study centre to ascertain the post-discharge survey data.

Whilst the patient remains on respiratory support (either NIV or ECCO_2_R), all patients will undergo daily assessment of dyspnoea and comfort, spirometry, electrical impedance tomography, parasternal electromyography and oesophageal pressure monitoring.

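### The economic outcome costs only ICU bed days and consumables, which is narrower than the promised UK healthcare-cost comparison; with EQ-5D named only at 3 months, the QALY rests on an assumed baseline

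*Protocol article*

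**What the plan says.** The last item in the protocol article's Secondary outcome section is "Cost-effectiveness with ICU bed day and consumables cost/quality adjusted life year (QALY". The numerator therefore has two components: ICU bed days and consumables.

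The abstract (Methods/design) describes the comparison more broadly: "Healthcare costs in the UK system will also be compared between the two groups". The Discussion motivates the economic work by what these patients cost the NHS in both critical care and the hospital.

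The Secondary outcome section also lists "Length of stay (ICU, hospital" and the rate of readmission to hospital within 3 months. Neither ward days nor readmissions are part of the cost definition.

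On the effect side, utility has one stated time point: "At 3-months following randomisation: COPD assessment test, St George’s Respiratory Questionnaire, EuroQoL 5D". The ECCO2R subsection gives the mode of collection at 3 months: "a telephone interview will be conducted by the randomising study centre to ascertain the post-discharge survey data". The Data collection section lists "basic demographic and medical details, including acute and chronic co-morbidity and medicines as well as a full physical examination", together with eligibility details and routine investigations, and names no utility measure. Survival is covered by "Mortality (ICU, hospital and 3 month" follow-up.

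**The concern.** The article promises one quantity and defines another. A comparison of healthcare costs should include the main places where the arms can differ. ECCO2R adds device consumables and may change how long patients stay in ICU, how long they stay on the ward and whether they come back. The stated definition covers the first two of these four and omits the last two. A reader of the result could take a difference in ICU and consumables cost for a difference in healthcare cost.

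The denominator raises a lesser question. A QALY is utility accumulated over time, and one end-point value does not fix the path that led to it. With 12 patients per arm, chance differences in starting utility may be as large as the effect, and they cannot be adjusted for unless they are measured.

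**Working it through.** The article states no cost, utility or QALY figure, so there is no economic figure of its own to reproduce.

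**Step 1: cost scope.** The components set against the text:

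| Component | Recorded as an outcome? | In the cost definition? |
|---|---|---|
| ICU bed days | Yes (ICU length of stay) | Yes |
| Consumables | Implied by the cost outcome | Yes |
| Ward days | Yes (hospital stay minus ICU stay) | No |
| 3-month readmissions | Yes (rate) | No |

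Write the between-arm difference in healthcare cost, for these components, as

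ΔC = ΔC(ICU) + ΔC(consumables) + ΔC(ward) + ΔC(readmission).

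The stated outcome is the sum of the first two terms. The gap is ΔC(ward) + ΔC(readmission), which is zero only if those terms are zero or cancel. Suppose, for illustration, that total stay is unchanged and one day moves from ward to ICU. The stated definition charges the full price of an ICU day, whereas the hospital's cost rises by the ICU price minus the ward price. The article gives no unit costs and no expected difference in ward days or readmissions, so neither the size nor the direction of the gap can be calculated.

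**Step 2: QALY per survivor.** The horizon is 3 months, or 0.25 year. With starting utility u0 and 3-month utility u3, and a straight line between them,

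QALY = 0.25 × (u0 + u3) / 2 = 0.125 × (u0 + u3).

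With u3 = 0.6 (assumption):

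- u0 = 0: 0.125 × 0.6 = 0.075
- u0 = 0.3: 0.125 × 0.9 = 0.1125
- u0 = 0.6: 0.125 × 1.2 = 0.150

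This twofold range concerns the absolute QALY of one patient, not the comparison between arms.

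**Step 3: between-arm difference.** Among survivors,

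ΔQ = 0.125 × (Δu3 + Δu0).

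A baseline common to both arms gives Δu0 = 0 and drops out. The results for assumed differences are:

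| Δu3 | Δu0 = −0.10 | Δu0 = 0 | Δu0 = +0.10 |
|---|---|---|---|
| 0.05 | −0.00625 | 0.00625 | 0.01875 |
| 0.10 | 0 | 0.0125 | 0.025 |

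A baseline gap of 0.1 in either direction thus shifts the difference by 0.125 × 0.1 = 0.0125 QALY. The assumed path matters too: carrying the 3-month utility back over the whole period gives 0.25 × 0.10 = 0.025 for Δu3 = 0.10, twice the straight-line value.

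**Step 4: is a gap of 0.1 plausible by chance?** With 12 per arm (Design section), the standard error of a baseline difference is SD × √(2/12). For a utility SD of 0.2, 0.25 or 0.3 (assumption) it is 0.082, 0.102 or 0.122. A gap of 0.1 is therefore about one standard error.

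**The case against.** The best defence is that the abstract is a summary and the Secondary outcome section specifies it. ICU bed days and consumables are UK healthcare costs, and the Discussion gives a motive rather than an outcome definition. Hospital stay and readmission will be reported in their own right, and limiting costs to the expected main drivers is a reasonable choice in a 24-patient physiology and feasibility trial. Baseline utility, valuation and perspective are commonly left to the full protocol or analysis plan, and the schedule figure, which is not shown, may include a baseline EQ-5D. Measuring utility at entry is also awkward in acutely ill patients on NIV who may lack capacity.

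Much of this stands, and it is why the baseline point is only a caveat. It does not remove the cost point. The article does not leave the cost components open: it fixes them, and more narrowly than the comparison it announces.

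A reader might infer more than the documents support:

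- *That cost per QALY cannot be obtained.* It can: 3-month mortality, one EQ-5D and a stated baseline assumption are enough to calculate it.
- *That the result would be wrong.* An ICU cost perspective is partial, not false. Whether it misleads depends on ward and readmission differences that the article does not give. Chance baseline imbalance in a randomised comparison is imprecision, not bias.
- *That patients who die would contribute no utility data.* The Statistical analysis section says that missing efficacy data are not filled in. It does not address utility after death, and death is a recorded outcome rather than a missing value.

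**Conclusion.** The point holds as a mismatch of scope on one secondary outcome. The defined cost covers ICU bed days and consumables, while the announced comparison is of healthcare costs and the stated motive includes hospital costs. Ward days and readmissions fall outside the definition although stay and readmission are already collected. The gap in money is unknown.

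The QALY's dependence on an assumed baseline is a caveat, and it rests on the visible text alone. Its size is 0.0125 QALY for each 0.1 of between-arm baseline gap, given a straight-line path over 0.25 year among survivors. The utilities, the gap and the SD range are all assumptions. The primary outcome and its analysis are untouched, so this is a worthwhile improvement rather than a serious defect.

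**What to change.** Make the cost definition and the announced comparison agree, in one of two ways:

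1. Extend the definition to hospital ward days and 3-month readmissions, valued at national unit costs. Stay and readmission are already recorded, so the downside is a little more costing work.
2. Keep the definition, and restrict the abstract's statement to ICU and consumables costs. This changes only wording.

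Option 1 is preferable because it lets the trial answer the cost question that it poses.

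For the QALY, state whether a baseline utility is available. If it is not, either present costs and 3-month EQ-5D side by side without a ratio, or report cost per QALY only under a stated baseline common to both arms, with a sensitivity range that includes between-arm gaps such as ±0.1. Neither needs new data. As the trial is recruiting, any protocol change goes through the sponsor and ethics committee approval that the Protocol amendments section describes.
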